## ADDITION-Leicester Objectives

The primary aim of the ADDITION-Leicester study is to evaluate the efficacy and cost-effectiveness of 1) a universal screening programme for T2DM and 2) intensive multi-factorial cardio-protection in those identified with T2DM within a UK multiethnic population. This objective will be achieved by determining the feasibility of screening as defined by the uptake and yield achievable within a primary care setting with a known 20-30% ethnic minority (Indo-Asian) presence. The health service and patient costs of screening for T2DM and other glucose abnormalities will be evaluated, together with objective assessments of five-year cardiovascular risk and mortality. ADDITION-Leicester is registered with ClinicalTrials.gov with identifier NCT00318032.

The study consists of two phases a screening phase, employing a universal gold standard diagnostic test for T2DM and an intervention phase, delivering a randomised trial of structured cardiovascular risk intervention in screen-detected cases.

A third element, the ADDITION-Leicester pre-diabetes cohort study prospectively assesses non-diabetes range fasting and post-challenge hyperglycaemia. The aim of the ADDITION-Leicester Prediabetes Cohort Study is to determine the annual rate of progression over five years of follow up and to characterise T2DM susceptibility phenotypes.

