
The size, geographical location and deprivation status of the 20 practices participating in ADDITION-Leicester is shown in Figure 1. Our calculated mean practice IMD scores match national survey deprivation quintiles and depicted practices within the Leicester city boundary appear typical of an urban UK deprivation distribution. To ensure all 20 sites are covered within the study timeframe, in six practices the entire eligible population have been sent information regarding the study whilst a random sample of the population are included in the remaining practices.

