### Phase 2: A randomised controlled trial of multifactorial intervention in individuals with screen-detected T2DM

Phase 2 is a pragmatic, cluster randomised, parallel group trial among people with screen-detected T2DM comparing intensive multi-factorial treatment with routine care in general practice according to national guidelines.

Randomisation is performed by an independent committee provided with practice demographics, deprivation status and approximate T2DM prevalence of individual practices. Practices and not individuals are randomised via a minimisation procedure with a 1:1 ratio. The screen detected T2DM control group (routine care arm) receive "usual care" within the primary care setting, according to national recommendations for management of T2DM and cardiovascular disease [38]. These participants will be reviewed one and five years post diagnosis, when anthropometric and biochemical data will be collected. The screen detected T2DM intervention group (intensive care arm) are introduced to dedicated, specialist physicians and nurses who provide a structured, intensified, protocol-driven, multi-factorial approach again within the primary care setting (table 2).

**Table 2 T2:** ADDITION-Leicester algorithm for the management of hyperglycaemia, hypertension and dyslipidaemia.

	Basic Treatment TARGET	add if above TARGET	add if above TARGET +BMI>19 or creatinine>130	Supplementary treatment If still above TARGET	
Blood Glucose	***HbA1c <6.5%*** SMBG Tuition DESMOND Dietary Advice	***HbA1c >6.5%*** SMBG Tuition DESMOND Biguanide	***HbA1c >6.5%*** SMBG Tuition DESMOND Insulin	***HbA1c >6.5%*** Biguanide Sulphonylureas Thiazolidinediones THEN Stop TZD Add basal Insulin (bedtime)	***HbA1c >6.5%*** ***and on *** ***Biguanide*** ***Sulphonylureas*** ***Insulin*** (basal/bolus) Intensify & titrate Insulin

Blood Pressure	***BP *** ***< 130/80 mmHg*** No treatment	***BP *** ***>130/80 mmHg*** ACE	***BP >135/80 mmHg*** ARB CCB Thiazide	***BP *** ***>130/80 mmHg*** ACE ARB/CCB	Thiazide alpha/beta Blocker

Cholesterol	***<3.5 mmol/L*** Diet	**>*3.5 mmol/L*** ***TG >6.0 mmol/L*** Diet Statin Consider Ezetimibe/Fibrate			

Aspirin	75 mg to all patients, unless contraindications of gastrointestinal bleeding, ulcers or haemophilia. If Aspirin contraindicated, consider Clopidogrel.				

KEY

**ACE**: Perindopril 2-4 mg daily or Ramipril 2.5-10 mg daily

**SMBG**: self-monitored blood glucose

**Biguanide: **Metformin 1-2 g daily

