#### Screening outcomes

Response and attendance characteristics (obtained from MPLs) will provide an objective assessment of screening within the invited population. The programme is of sufficient size to enable the feasibility and complexities of screening to be stratified by ethnicity and socio-economic status. Outcomes will include the number of individuals responding to first and second mailers, presenting for screening, and subsequently diagnosed with T2DM or IGR. Metabolic dysfunction, cardiovascular risk, psychological status and self-perceived health in newly diagnosed T2DM and IGR will be determined. Population effects of screening will be determined via Office of National Statistics (ONS) mortality tagging and self-report health questionnaires five years after screening. Response and attendance rates will also be compared with previous population T2DM screening studies to enable specific conclusions to be drawn about the ADDITION-Leicester population [25,29].

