### Statistical methods and power calculation

Assuming a prevalence of screen-detected diabetes of 4.5%, we calculated a target of 7,000 (30% (2,100) South Asians) volunteers over three years sufficient to identify a screen-detected T2DM cohort (n = 225) demonstrating a 6% difference (80% power, alpha 0.05) between routine and intensive groups at one year assuming an intra cluster correlation coefficient of 0.14 and allowing for a loss to follow-up of 15%.

The benefits of screening and intensive treatment will be assessed using an intention to treat and allowing for clustering of patients by practice. The UKPDS CHD score at 5 years will be compared along with all secondary outcomes by treatment group, adjusting for differences in baseline variables. Estimates will be presented with 95% confidence intervals to reflect uncertainty in estimations. Sensitivity analysis assuming a range of outcomes for non-completers will be informed by baseline data. The primary perspective for the cost analysis will be the health service, with personal costs as a secondary perspective. The costs of intensive intervention will be compared with unit change in health utility at one year. Costs at one year and future costs derived from existing data will be compared with modelled risk of death and cardiovascular events, with appropriate sensitivity analysis. The cost of screening and the screening plus intensive treatment will be compared with changes in health utility from questionnaire data.

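### The benefit of screening is to be assessed by intention to treat and mortality tagging, but everyone randomised was screen-detected and no unscreened comparator is named, so only treatment effect, uptake, yield and cost can be estimated

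*Protocol article*

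**What the plan says.** All references are to the protocol article.

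- *ADDITION-Leicester Objectives*: the primary aim is "to evaluate the efficacy and cost-effectiveness of 1) a universal screening programme for T2DM", with intensive treatment as the second item. The next sentence narrows it: "This objective will be achieved by determining the feasibility of screening as defined by the uptake and yield achievable". The section then adds costs, "together with objective assessments of five-year cardiovascular risk and mortality".
- *Abstract, Discussion paragraph*: efficacy of screening is named beside feasibility as something that will inform national policy.
- *Screening outcomes*: "Population effects of screening will be determined via Office of National Statistics (ONS) mortality tagging" and self-report questionnaires five years after screening. The only outside comparison named there is of response and attendance rates with earlier screening studies.
- *Phase 2*: the trial is a "cluster randomised, parallel group trial among people with screen-detected T2DM comparing intensive multi-factorial treatment with routine care in general practice". Practices are the unit of randomisation.
- *Secondary and intermediate outcomes*: all-cause mortality comes from tagging participants.
- *Statistical methods and power calculation*: "The benefits of screening and intensive treatment will be assessed using an intention to treat", allowing for clustering by practice. The comparison then specified is by treatment group, and the power calculation is for routine versus intensive care. The last sentence sets the cost of screening, and of screening plus intensive treatment, against change in health utility from questionnaires.

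**The concern.** Intention to treat is a rule for analysing people by the arm to which they were randomised. It can support a statement about the benefit of screening only if screening, or the invitation to it, was what was randomised. Here it was not. Similarly, tagging a cohort of screened volunteers gives a death rate. It becomes an effect only when set against the rate expected without screening, and no source for that second rate is named.

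The article states that its results are meant for screening policy, and its introduction acknowledges that there is little evidence that screening improves outcomes. A result presented as an intention-to-treat assessment of screening would carry the authority of a randomised comparison that was never made.

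**Working it through.** No figure in the article depends on this point, so there is nothing to reproduce. The check is whether each promised quantity has the contrast that it needs.

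**1. The randomised contrast.** Write the expected outcome in an arm as *m + s + t*. Here *m* is the outcome without screening, *s* the effect of having been screened, and *t* the effect of intensive rather than routine care among screen-detected cases.

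- Intensive arm: *m + s + t*
- Routine arm: *m + s*
- Difference: *(m + s + t) − (m + s) = t*

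The term *s* cancels whatever its value. Sample size and intracluster correlation affect the precision of *t*, but neither brings *s* back.

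**2. Mortality and health status at five years.** The effect of screening is the risk with screening minus the risk without it. Tagging and questionnaires in screened people supply the first term. The second is not observed in any group that the article names.

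**3. Utility.** The change from baseline in screened people mixes any effect of screening with ageing, disease progression and care received over the same period. Without a concurrent unscreened group these cannot be separated.

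**4. Promise against design.**

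| Quantity | Contrast or denominator needed | Available as described? |
|---|---|---|
| Intensive v routine treatment | Randomised practices | Yes |
| Uptake | Responders and attenders over invited | Yes |
| Yield | Cases found over attenders or invited | Yes |
| Cost per case detected | Screening cost over cases found | Yes |
| Benefit of screening by intention to treat | Screened v unscreened by allocation | No |
| Population effect on mortality or health status | Same, or a named external rate | No |
| Cost of screening per unit of utility gained | Utility with v without screening | No |

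The *Yes* rows are real outputs. For example, *Funding and timescale* reports 345 new cases from over 35,000 invitations, a yield of at most 345 / 35,000 = 0.99% per person invited.

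**The case against.** **The aim is already defined as feasibility.** This is the strongest defence, and much of it stands. The objectives section says that the aim will be met through uptake and yield, and the outcomes listed later match. A reader might infer that the whole screening half of the primary aim cannot be estimated. The document does not support that, because uptake, yield and cost are all estimable. The definition does not cover the later statements, however. Uptake and yield measure neither a benefit assessed by intention to treat nor a population effect determined by mortality tagging.

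**It is loose wording about a package.** The sentence could mean the joint benefit of screening followed by intensive treatment. That reading also needs people who were not screened.

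**The full protocol or analysis plan may name a comparator, or a decision model may supply a no-screening arm.** Either is possible, and the article does mention modelled risk for the costing of treatment. But no later document can turn a randomisation between treatments into one between screening and no screening. The utility sentence also draws on questionnaire data, not on a model.

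**Biased mortality comparisons.** A reader might infer that the trial will compare deaths in attenders with deaths in non-attenders or in earlier studies. The article proposes neither. It plans to compare responder and non-responder characteristics and, externally, response and attendance rates. The fair criticism is that no mortality comparator is named, not that a biased one was chosen.

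**A randomised comparator already exists.** Six of the 20 practices invited everyone eligible, while "a random sample of the population are included in the remaining practices". A reader might infer that invited versus uninvited people in those 14 practices already give a valid test of screening. The document does not support this as a ready analysis. It gives uninvited people no role and describes no follow-up of them. Tagging is of participants, and practice lists extracted before invitation cannot hold deaths over the next five years. Dilution would also be severe. If diagnosed cases died at the average rate (an assumption), preventing every death among them would lower mortality in the invited group by only about 1%, since they are about 1% of it.

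**Conclusion.** The point holds for the benefit, or efficacy, of screening and no further. As written, the article attaches an intention-to-treat label and a claim of population effects to a quantity that its design does not identify. The shortfall is one of identification, not precision, so it has no numerical size: the randomised difference carries no information on screening at any sample size.

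The conclusion rests on two readings: that the Phase 2 randomisation is the only one intended for analysis, and that mortality tagging covers participants, as the secondary outcomes section says. The primary endpoint, the power calculation, the comparison of intensive with routine care, and the feasibility results all stand.

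**What to change.** 1. *Statistical methods and power calculation*: confine the intention-to-treat statement to intensive versus routine treatment among screen-detected cases.
2. *ADDITION-Leicester Objectives* and the *Discussion* paragraph of the abstract: replace efficacy of screening with feasibility, uptake, yield and cost per case detected, in line with the definition that the objectives section already gives.
3. *Screening outcomes* and the last sentence of *Statistical methods and power calculation*: describe five-year mortality, health status and utility change in screened participants as descriptive, not as effects of screening.

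These are changes of wording. They need no new data, participants or analysis. The cost is a narrower claim: the study would inform policy on whether universal screening is feasible, what it finds and what it costs, and on whether intensive treatment helps those found, but not on whether screening itself improves outcomes.

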**Methods:**

ADDITION-Leicester consists of community-based screening and intervention phases within 20 general practices coordinated from a single academic research centre. Screening adopts a universal diagnostic approach via repeated 75g-Oral Glucose Tolerance Tests within an eligible non-diabetic population of 66,320 individuals aged 40-75 years (25-75 years South Asian). Volunteers also provide detailed medical and family histories; complete health questionnaires, undergo anthropometric measures, lipid profiling and a proteinuria assessment. Primary outcome is reduction in modelled Coronary Heart Disease (UKPDS CHD) risk at five years. Seven thousand (30% of South Asian ethnic origin) volunteers over three years will be recruited to identify a screen-detected T2DM cohort (n = 285) powered to detected a 6% relative difference (80% power, alpha 0.05) between treatment groups at one year. Randomisation will occur at practice-level with newly diagnosed T2DM cases receiving either conventional (according to current national guidelines) or intensive (algorithmic target-driven multi-factorial cardiovascular risk intervention) treatments.

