### Endpoints and outcomes

#### Primary endpoint

The primary endpoint is reduction in modelled coronary heart disease at five years using the United Kingdom Prospective Diabetes Study (UKPDS CHD) risk equation [43]. The UKPDS CHD risk engine has the advantage of being diabetes specific and incorporates an adjustment for the effects of south Asian ethnicity when calculating CHD risk. It has recently been shown to be as accurate as other CHD risk assessment tools in T2DM and has been validated for the effects of ethnicity [43].

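### The primary analysis ties covariate adjustment to observed baseline differences and does not commit to the baseline UKPDS CHD score or the practice factors behind the minimisation

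*Protocol article*

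**What the plan says.** The section on statistical methods and power calculation describes the main comparison in two steps. The analysis is to be done "using an intention to treat and allowing for clustering of patients by practice". Then: "The UKPDS CHD score at 5 years will be compared along with all secondary outcomes by treatment group, adjusting for differences in baseline variables". No covariate is named, and no threshold or selection procedure is given.

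The Phase 2 section describes the allocation: "Practices and not individuals are randomised via a minimisation procedure with a 1:1 ratio". The committee responsible is "provided with practice demographics, deprivation status and approximate T2DM prevalence of individual practices". These are the apparent minimisation factors, although the article does not list them under that name.

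The primary endpoint section words the outcome as a reduction: "The primary endpoint is reduction in modelled coronary heart disease at five years". The methods section compares the five-year score itself. Everything in the article rests on 20 practices (abstract, methods paragraph).

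**The concern.** Covariates earn their place by predicting the outcome. An observed difference between arms is a poor guide to that. The obvious predictor of the five-year UKPDS CHD score is the same score at baseline, and the screening visit already collects blood pressure, lipids, HbA1c, smoking status and ethnicity. Under a rule driven by differences, that score is used only in the unlucky samples where the arms diverge on it. In all other samples its predictive value is discarded.

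The rule also works against the design. Minimisation makes the factors it uses less likely to differ between arms, so a rule based on differences tends to leave out the variables on which the allocation was balanced. If those factors predict the outcome, leaving them out tends to give standard errors that are too wide.

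Precision is scarce in a trial of 20 clusters with a sizeable ICC. A fixed baseline covariate would also settle how baseline risk enters the endpoint, because the adjusted treatment effect is the same whether the outcome is the five-year score or its change from baseline.

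**Working it through.** **Inputs from the article.** 20 practices; ICC 0.14; n = 225 (statistical methods) or n = 285 (abstract); 80% power; alpha 0.05, taken as two-sided because the article does not say.

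**Assumptions, not in the article.** Correlation r between baseline and five-year score of 0.5, 0.7 or 0.8; equal practice sizes.

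**The plan's own figure.** The cohort size cannot be rebuilt, because no SD or mean risk is given. Only the implied precision can be shown.

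- n = 225: patients per practice m = 225/20 = 11.25; design effect 1 + (11.25 − 1) × 0.14 = 2.435; effective n = 225/2.435 = 92.
- n = 285: m = 14.25; design effect 1 + 13.25 × 0.14 = 2.855; effective n = 285/2.855 = 100.
- Detectable standardised difference at n = 225: (1.96 + 0.84) × √(4/92.4) = 0.58.

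**Gain from always adjusting (normal approximation).** The standard error is multiplied by √(1 − r²). For r = 0.5/0.7/0.8 this is 0.87/0.71/0.60. An effect with 80% power unadjusted then has 90%/97.5%/99.7%.

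**Simulation of the rule.** Practice means were generated for 20 practices of 11 patients, ICC 0.14, 20,000 runs per setting, with a true standardised effect of 0 or 0.6. The correlation r was applied to the practice means, so baseline risk predicts equally well at both levels. Tests used the t distribution on between-practice degrees of freedom. The baseline score was the only covariate; the minimisation factors were not simulated.

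| | r = 0.5 | r = 0.7 | r = 0.8 |
|---|---|---|---|
| Power, unadjusted | 78.2% | 77.1% | 77.9% |
| Power, adjust only if baseline p<0.05 | 78.5% | 78.6% | 79.9% |
| Power, adjust only if baseline p<0.20 | 79.8% | 82.5% | 84.6% |
| Power, always adjust | 86.3% | 95.6% | 99.1% |
| Type I error, p<0.05 trigger | 4.7% | 3.8% | 3.3% |
| Type I error, p<0.20 trigger | 4.1% | 2.8% | 2.0% |
| Type I error, always adjust | 5.3% | 5.2% | 4.9% |

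Share of the available power gain kept by the p<0.05 trigger: (78.5 − 78.2)/(86.3 − 78.2) = 4% at r = 0.5, and (79.9 − 77.9)/(99.1 − 77.9) = 9% at r = 0.8. The looser p<0.20 trigger keeps (79.8 − 78.2)/(86.3 − 78.2) = 20% and (84.6 − 77.9)/(99.1 − 77.9) = 32%.

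The mean estimate under the triggers was 0.599 to 0.602 for a true 0.6.

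**How far the gain depends on the practice level.** With total variance 1, the variance of a practice mean is 0.14 + 0.86/11.25 = 0.216, of which 0.14/0.216 = 65% lies between practices. If the baseline score explains patient-level variance only, this becomes 0.14 + (1 − r²) × 0.86/11.25:

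- r = 0.5: 0.197, a fall of 9%; standard error × 0.955; power 80% becomes about 83–84%.
- r = 0.8: 0.168, a fall of 23%; standard error × 0.88; power 80% becomes about 89%.

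**The case against.** The strongest reply is that the phrase may mean no more than ordinary adjustment for baseline values, and that a journal article commonly leaves the covariate list, the model form and the degrees of freedom to a fuller document. The missing list is indeed no fault, and the benign reading cannot be excluded. But the sentence does more than omit a list. It states a principle for choosing covariates, and an analysis plan that followed it would inherit the weakness. If ordinary adjustment was meant, one sentence can say so.

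Four stronger readings are tempting, and the documents do not support them:

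- A reader might infer that the plan leaves out the minimisation factors. It excludes nothing; those factors are themselves baseline variables. It only fails to commit to them.
- A reader might infer bias. Mechanical selection on imbalance gave none in the simulation. Bias would need discretionary selection with outcomes known, which the article does not describe.
- A reader might infer a test that is too liberal with 10 practices per arm. Comparing a t statistic on 18 degrees of freedom with 1.96 would give 6.6%, but the article specifies no normal reference distribution, and the imbalance rule itself errs towards conservatism.
- A reader might turn residual variances of 1 − r² into a multiplier of 1.3 to 2.8 on the number of patients. With the number of practices fixed, more patients reduce only the 0.86/m term, so that equivalence fails here.

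The wording of the endpoint as a reduction is weak evidence by itself, since it may simply mean a between-group difference at five years.

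**Conclusion.** The point holds as a weakness in the stated adjustment rule, on the natural reading of the sentence. The consequence is lost power and a conservative test; the primary analysis is not invalid. Under the assumed correlations at both levels, adjusting only on imbalance at p<0.05 leaves power about where it is without adjustment (78–80%), against 86–99% with a fixed baseline covariate, and type I error falls to 3.3–4.7%. These figures rest on assumed correlations and equal practice sizes. If baseline risk predicts only within practices, the benefit of always adjusting shrinks to a rise from 80% to roughly 83–89%. The direction is the same throughout. The cost of ignoring the minimisation factors was not quantified.

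**What to change.** In the statistical methods section, replace the closing phrase on baseline differences with: *adjusted, whatever the observed imbalance, for the participant's baseline UKPDS CHD score and a small prespecified set of the practice factors used in minimisation, allowing for clustering by practice*. Add that each secondary outcome with a baseline measurement is adjusted for its own baseline value.

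The set of practice factors should be kept short and named. Practice demographics could expand into several terms, and there are only 18 between-practice degrees of freedom to spend. Small-sample degrees of freedom are sensible in the same sentence. The change needs no new data: the baseline score can be computed from the screening visit and the practice factors were supplied for the allocation. The cost is a few between-practice degrees of freedom.
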